### Withdrawals

Participants are free to withdraw from the trial at any point. All withdrawals will be recorded on a standardised form. Those who withdraw from the trial will be asked if they would be willing to discuss their reasons for withdrawal to allow the identification of any barriers to participation and highlight whether measures to facilitate participation in the trial need to be implemented.

### Qualitative study

After the 12-month follow-up, a purposive sample of up to 30 participants from the intervention group will be interviewed about the STAR care pathway. This sample size should be sufficient to achieve data saturation in keeping with standards of qualitative research [55, 56]. Interviews will address participants’ experiences of the pathway and their experience of surgery, pain, and resource use. With participants’ consent, interviews will be audio-recorded and anonymised transcripts imported into QSR NVivo™ and analysed using a thematic approach [54]. Findings will be used to further inform the interpretation of the trial’s findings as well as implementation into clinical practice.

### Thank you cards and newsletters

Cards will be sent to participants at 3 and 9 months after randomisation to thank them for their continuing involvement in the STAR trial and to remind them when they can expect to receive the next STAR questionnaire. Newsletters will be sent to all participants every 6–12 months to keep them updated on trial progress.

### Sample size

For a 2:1 intervention:control randomisation ratio, a sample size of 285 patients would have a power of 80% to 90% to detect standardised differences of between 0.35 and 0.40 standard deviations using a two-sided 5% significance level. From previous studies [57, 58], the standard deviations for each of the BPI Interference and Pain Severity scales for patients with chronic post-surgical pain have been observed to be approximately 2, in which case, the target effect size translates to a difference between intervention and control groups of between 0.7 and 0.8 scale points for both scales. Such a difference is worthwhile detecting clinically, since the current consensus statement indicates that differences of approximately one scale point can be deemed the minimally important difference for both of these scales [58, 59]. To allow for a conservative 25% loss to follow-up in the STAR trial, 381 participants will be recruited.

### Data management

Participants’ personal data will be regarded as strictly confidential and will be entered onto a secure administrative Microsoft Access™ database stored on a University of Bristol server. Only STAR team members with appropriate contracts/letters of access with NHS trusts will have access to participants’ personal data. Anonymised trial data will be stored using REDCap, an online secure application [60]. REDCap will also be used to administer online questionnaires to trial participants. Double data entry of the primary outcome measure for all participants completing paper questionnaires and full Case Report Forms for a random sample of participants will be undertaken to ensure data quality.

### Data monitoring

The trial will be overseen by an independent Trial Steering Committee (TSC), composed of four clinical or non-clinical academics and one member of the public. The TSC will meet at regular intervals to review trial progress, protocol adherence and patient safety. The TSC decided that a Data Monitoring Committee was not necessary for this trial and that safety data and data quality will be reviewed by the TSC. No formal interim analysis will be conducted; however, data from the pilot phase were analysed to evaluate the feasibility of proceeding to the main trial. The trial will be stopped earlier than planned if mandated by the NHS Ethics Committee, recommended by the TSC, funding for the trial ceases or for any other relevant major clinical or therapeutic reason.

### Auditing

The coordinating centre will regularly monitor trial sites to ensure data quality and completeness. The trial sponsor (North Bristol NHS Trust) will monitor the trial, potentially including reviewing the Site Files and participants’ medical records.

### Statistical analysis

The full statistical analysis plan for the STAR trial can be accessed at the University of Bristol publications repository [61]. Data analysis will be conducted in accordance with CONSORT guidelines, commencing with descriptive analyses to compare groups at baseline. The primary comparative analysis will apply the intention-to-treat principle including all participants as randomized and with primary outcome data available at 12 months after randomisation. The mean BPI pain severity and BPI interference scores at 12 months after randomisation will be compared between the usual care and intervention groups using linear regression models, adjusting for the respective baseline score and the minimisation/stratification variables. Sensitivity analyses will use standard imputation techniques to impute missing primary outcome data. The secondary outcomes will be analysed using regression models in a similar manner to the primary analysis. Subgroup analyses will investigate variation in the treatment effect between orthopaedic centres and by pain severity, using interaction terms added to the regression models. Explanatory analyses, such as Complier Average Causal Effect methodology, will be used to estimate the effect in those patients able to comply with their allocated intervention. Compliance in the intervention group is defined as attendance at the STAR assessment clinic.

### Cost-effectiveness analysis

The primary cost-effectiveness analysis will take an NHS and Personal Social Services perspective. A secondary analysis will take a broader perspective to include patients’ costs. Only resources used in relation to the treatment of chronic pain will be measured from randomisation to 12 months follow-up. All resources will be valued using routine data sources and information from hospital finance departments. All analyses will be on an intention-to-treat basis and there will be no discounting of costs or effects given the 1 year duration of the study. The primary outcome for the economic evaluation will be the Quality Adjusted Life Year (QALY). The difference in costs and QALYs between the arms will be assessed using the Net Benefit framework using appropriate regression models adjusted for baseline values of the minimisation/stratification variables. Additionally, the difference in costs and those in primary outcomes will be examined. If no arm is dominant, then incremental cost-effectiveness ratios will be calculated using, if appropriate, Seemingly Unrelated Regressions to account for the potential correlation between costs and the primary outcomes. Given the number of important secondary outcomes, a cost consequence analysis will also be conducted in relation to these outcomes. Uncertainty will be addressed using cost-effectiveness acceptability curves and sensitivity analyses.

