### Randomisation

After participants have provided written, informed consent and have returned a completed baseline questionnaire, they will be randomly allocated to the STAR pathway or usual care. Participants will be informed of their allocation by a member of the research team. Randomisation occurs as soon as possible after the baseline questionnaire is received. Randomisation with allocation concealment is conducted remotely via the Bristol Randomised Trials Collaboration using a web-based randomisation system. Randomisation takes place on a 2:1 basis to ensure that the intervention service is running at sufficient capacity to enable a pragmatic assessment of its clinical and cost-effectiveness. Moreover, if the intervention is operating to a sufficient degree of capacity, then per-protocol and Complier Average Causal Effect analyses will be more reliable and have higher power. To ensure reasonable balance between the two treatment groups, allocation is minimised by pain severity and pain interference scores for the replaced knee (assessed with the Brief Pain Inventory Severity and Interference Scales and categorised into tertiles based on data from a previous study [30]), and stratified by trial centre.

Blinding of participants and trial personnel to treatment allocation is not possible due to the nature of the intervention. After participants have been randomised, the research team will send the participant and their General Practitioner (GP) a letter to inform them of treatment allocation.

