### Outcome measurement

All participants are assessed at baseline prior to randomisation (3 months after surgery) and at 6 months (9 months after surgery) and 12 months (15 months after surgery) after randomisation. All outcome measurements will be undertaken via self-report questionnaires and participants are provided with a complimentary teabag with each questionnaire. Participants are offered the option of completing study questionnaires on paper or online through REDCap (https://www.project-redcap.org/). If completed questionnaires are not received within 2 weeks, a reminder questionnaire will be sent. If no response is received to the reminder, a researcher will telephone the participant to offer support in completing the questionnaire on the telephone. Telephone calls to participants who do not return a follow-up questionnaire will be performed by a researcher from a different trial centre to ensure that the researcher is blinded to treatment allocation.

The primary and secondary outcomes map directly onto the eight domains of the core outcome set for the assessment of chronic pain after knee replacement [45]. Details of the time point for each outcome are provided in Fig 1. The co-primary outcomes are pain severity and pain interference assessed using the BPI [38] at 12 months after randomisation. Participants will be asked to complete the BPI in relation to their operated knee. Secondary outcomes include:Pain and physical functioning: OKS [35]Neuropathic pain: PainDETECT [40] and DN4 [41]Psychological status: HADS [39], Pain Catastrophizing Scale [46], and Possible Solutions to Pain Questionnaire [47]Use of pain medications: Resource use questions (to be analysed as part of the cost-effectiveness analysis)Improvement and satisfaction with pain relief: Self-Administered Patient Satisfaction Scale [48], single-item question on comparison of pain to pre-operative painTemporal aspects of pain: Single-item questions on pain frequency during past 24 h and 4 weeks.Capability: ICECAP-A [49]Health-related quality of life: EQ-5D-5 L [50] and Short Form-12 [51]Pain elsewhere: body diagram to assess chronic widespread pain [52]

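### The covariates stated for the QALY and net-benefit regressions do not include baseline utility, although the clinical models adjust for each outcome's own baseline score

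*Protocol article*

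**What the plan says.** The Cost-effectiveness analysis section makes the QALY the primary outcome of the economic evaluation. It states that differences in costs and QALYs will be assessed "using the Net Benefit framework using appropriate regression models adjusted for baseline values of the minimisation/stratification variables".

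The Randomisation section says what those variables are: "allocation is minimised by pain severity and pain interference scores for the replaced knee", which for allocation are "categorised into tertiles based on data from a previous study", with allocation also "stratified by trial centre".

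For the co-primary BPI outcomes, the Statistical analysis section specifies regression "adjusting for the respective baseline score and the minimisation/stratification variables". It then adds: "The secondary outcomes will be analysed using regression models in a similar manner to the primary analysis".

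The Outcome measurement section says that all participants are assessed before randomisation and again at 6 and 12 months. It lists the EQ-5D-5L and the SF-12 as the measures of health-related quality of life. The article does not say which of them supplies the utilities or how the QALY is calculated.

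**The concern.** The clinical models carry two kinds of covariate: the outcome's own baseline value, and the variables used in allocation. The economic models, as described, carry only the second kind. The EQ-5D-5L analysed as a secondary clinical outcome would therefore presumably be adjusted for its own baseline, while a QALY built from the same instrument would not.

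The gap matters more for a QALY than for an ordinary follow-up score. In an area-under-the-curve QALY the baseline utility enters the outcome itself, before any treatment effect is possible, and it also predicts the later utilities. Allocation was balanced on knee pain, so the part of general health utility that knee pain does not explain is left to chance. Cost-effectiveness is a stated objective and is meant to inform commissioning, so the precision of the incremental QALY, and its freedom from chance imbalance, are worth protecting.

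**Working it through.** **The passages side by side**

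| Model | Own baseline value | Minimisation/stratification variables |
|---|---|---|
| BPI severity and interference | named | named |
| Secondary clinical outcomes | implied (similar manner) | implied |
| Costs, QALYs, net benefit | utility not named | named |

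No other section adds baseline utility to the economic models.

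**Numbers analysed.** The Sample size section plans on 285 at 2:1, so 285 × 2/3 = 190 and 285 × 1/3 = 95. That section's own figures reproduce to rounding: power is 79.5% for 0.35 SD and 88.9% for 0.40 SD, against the stated 80% to 90%, and 285/0.75 = 380, against 381 recruited. The present point does not depend on them.

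**Assumed inputs (none is in the documents).** Utility SD s = 0.20–0.30, equal at all visits. Correlation of baseline with 6- and 12-month utility r = 0.3–0.7. Correlation between 6 and 12 months 0.7. Share of baseline utility variance explained by BPI and centre R² = 0–0.5, with these covariates related to later utility only through baseline utility.

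1. Trapezium QALY over one year: 0.5 × (u0 + u6)/2 + 0.5 × (u6 + u12)/2 = 0.25·u0 + 0.5·u6 + 0.25·u12.
2. Slope of the QALY on baseline utility: b = 0.25 + 0.75r, which is 0.475, 0.625 and 0.775 for r = 0.3, 0.5 and 0.7.
3. SE of the baseline imbalance left after BPI and centre: s × √(1 − R²) × √(1/190 + 1/95), where the last factor is 0.1257.
4. Shift in the QALY difference: b times that imbalance.

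| Case | s | r | R² | Imbalance, 1 SE | QALY shift, 1 SE | QALY shift, 1.96 SE |
|---|---|---|---|---|---|---|
| Smallest | 0.20 | 0.3 | 0.5 | 0.0178 | 0.0084 | 0.0165 |
| Middle | 0.25 | 0.5 | 0.25 | 0.0272 | 0.0170 | 0.0333 |
| Largest | 0.30 | 0.7 | 0 | 0.0377 | 0.0292 | 0.0573 |

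5. Precision. In units of s², the QALY variance is V = 0.55 + 0.375r. It is V − R²b² given BPI and centre, and V − b² once baseline utility is added.
   - Middle case: (0.7375 − 0.3906)/(0.7375 − 0.0977) = 0.3469/0.6398 = 0.54. The SE of the QALY difference falls from 0.0251 to 0.0185.
   - Largest gain (r = 0.7, R² = 0): (0.8125 − 0.6006)/0.8125 = 0.26.
   - Smallest gain (r = 0.3, R² = 0.5): (0.6625 − 0.2256)/(0.6625 − 0.1128) = 0.79.

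**Sensitivity check.** Let BPI also predict later utility directly. Take s = 0.25, r = 0.5–0.7, BPI–baseline utility correlation ρ = 0.5–0.7, BPI–later utility correlation k = 0.3–0.5 (absolute values), and all 381 recruited (254 v 127). The slope given BPI is [0.25 + 0.75r − ρ(0.25ρ + 0.75k)]/(1 − ρ²). It runs from (0.625 − 0.7 × 0.55)/0.51 = 0.47 to (0.775 − 0.7 × 0.40)/0.51 = 0.97. The one-SE shift is 0.009–0.019 and the variance ratio 0.26–0.74, both inside the ranges above.

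**The case against.** The article does not say that its list is complete. It speaks of appropriate regression models adjusted for these variables, in one condensed paragraph, and it promises unspecified sensitivity analyses. A fuller health-economic plan, not shown, may name baseline utility. This limits the claim: a reader might infer that the models adjust for BPI and centre and nothing else, but the text supports only that the set it states does not include baseline utility. The objection does not remove the point. The article chose to name the covariates, and in the preceding section it did name the baseline score.

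A reader might also infer that the economic models use BPI in tertiles. The tertiles are stated for allocation; the economic section speaks of baseline values, which may be the continuous scores. Utility is absent either way.

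Nor does an imbalance pass whole into the result. BPI adjustment first removes the part related to pain, and in the main illustration 0.475–0.775 of the remainder carries over. Randomisation keeps the estimator free of systematic bias, and an ordinary confidence interval already reflects the chance variation. What stands is avoidable conditional error and a wider interval than necessary.

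Finally, the premises are partly inferred. The trapezium method and the EQ-5D-5L as utility source are presumed. Baseline collection is inferred from the Outcome measurement section, because the schedule figure is not shown. The Appendix lists the EQ-5D-5L at 3, 6 and 12 months after randomisation. If a 3-month value really entered the curve, the direct weight of baseline utility would be 0.25/2 = 0.125 instead of 0.25. It would be smaller, but baseline utility would still be part of the outcome.

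**Conclusion.** The point holds in this form: the stated covariate set for the QALY and net-benefit regressions leaves out baseline utility, out of step with the article's own rule for clinical outcomes. The consequence is partial carry-over of chance imbalance and lost precision in the primary economic outcome, not systematic bias.

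The sizes are illustrative only: about 0.008–0.029 QALYs for a one-SE imbalance, and a variance of about 0.26–0.79 of its value once baseline utility is added. They rest wholly on the assumed SD, correlations and R², and on a trapezium QALY. They should not be read as figures for this trial, and the documents give no cost-effectiveness threshold with which to turn them into money.

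Confidence is moderate to high: high on what the text states and on the direction of the effect, lower because any fuller economic plan and the schedule figure cannot be seen. It is an improvement that should be made, not a flaw that invalidates the economic evaluation.

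**What to change.** Add baseline utility, from the instrument used for the QALY (presumed EQ-5D-5L), as a covariate in the QALY and net-benefit regression models. Keep BPI severity, BPI interference and centre. State how the QALY is calculated and from which instrument, and confirm that this instrument is in the questionnaire completed before randomisation.

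The change need not extend to every economic model. Where costs are set against BPI, the baseline BPI scores are already among the named variables, so adding them again helps only if tertiles were meant. The Seemingly Unrelated Regressions are described for costs and the primary outcomes, most naturally BPI, and the area-under-the-curve argument does not reach them.

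The cost is about one sentence in the economic analysis plan, fixed before the outcome data are analysed. It needs no new data if the instrument is in the baseline questionnaire, and no change to the sample size.

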### Dissemination policy

Publications will include a final report, presentations at scientific meetings and open-access articles in peer-reviewed journals. Avenues for disseminating findings to patients and the public will be identified and developed in collaboration with the PEP-R patient involvement groups and relevant charity organisations such as Arthritis Care. In addition, all participants who indicate that they wish to receive study results will be sent a plain English summary of the final results.

## Discussion

To our knowledge, this is the first randomised controlled trial to evaluate the clinical and cost-effectiveness of a care pathway when compared with usual care for patients screened as having early indications of chronic pain after total knee replacement. The care pathway aims to identify the potential causes of pain to enable early appropriate onwards referral to existing services for targeted and individualised treatment to improve pain management and to reduce the impact of pain. The design and development of this complex intervention has been informed by multiple stages of work [30], in line with Medical Research Council guidance on the development of complex interventions [62].

There are practical and operational issues pertinent to this trial, particularly regarding screening and randomisation of patients. Approximately 1 in 5 patients experience chronic pain after total knee replacement and therefore this trial involves a stage of screening to identify this subgroup early in the postoperative period. An issue is that patients with poorer outcomes after joint replacement are less likely to respond to postal questionnaires [63]. A Cochrane review identified a number of strategies to improve response rates to questionnaires [64], and we have implemented a number of these, including pre-notification screening cards and non-monetary incentives in the form of a teabag to indicate that the study team appreciate that completion of trial questionnaires requires time and effort from the participant.

In this trial, we are randomising patients on a 2:1 intervention:control allocation ratio. Justification for the use of unequal randomisation allocation is often poorly reported [65]. There are numerous reasons given for the use of unequal randomisation ratios, including to reduce costs, improve recruitment, increase the amount of information on the new treatment including safety data, and to account for differential loss to follow-up and cross-over [65–67]. In this trial, randomisation will take place on a 2:1 basis to ensure that the intervention service is running at sufficient capacity to enable a pragmatic assessment of its effectiveness and, particularly, cost-effectiveness. Providing potential participants with an explanation for the reasons behind 2:1 randomisation is important to ensure that equipoise is conveyed adequately. To address this concern, we are undertaking patient involvement activities and qualitative research within the internal pilot phase with the aim of improving the verbal and written information we provide to potential participants about randomisation.

The findings of this trial will provide evidence to guide decisions by clinicians, policymakers and patients, and to inform commissioning of services. If shown to be clinically and cost-effective, this intervention could improve the early identification and management of chronic pain after total knee replacement. It is also possible that this model of care delivery could be adapted for the evaluation of the management of chronic post-surgical pain in other surgical contexts.

### Trial status

The first participant was recruited into the trial in October 2016. Recruitment is scheduled to be completed by March 2019, and follow-up and data collection are scheduled to be completed by March 2020.

## Appendix

**Table 1 Tab1:** World Health Organization Trial Registration Data Set

Item number	Item	Description
1	Primary registry and trial identifying number	ISRCTN92545361
2	Date of registration in primary registry	30/08/2016
3	Secondary identifying numbers	REC reference: 16/SW/0154 NIHR Programme Grant for Applied Research reference: RP-PG-0613-20,001
4	Sources of monetary or material support	NIHR Programme Grant for Applied Research
5	Primary sponsor	North Bristol NHS Trust Research and Innovation, [name] [contact] E-mail: [contact]
6	Secondary sponsor	Not applicable
7	Contact for public queries	[name] Musculoskeletal Research Unit, Translational Health Sciences, Bristol Medical School, University of Bristol [name] [contact] E-mail: [contact]
8	Contact for scientific queries	As above
9	Public title	Evaluation of a care pathway for patients with long-term pain after knee replacement
10	Scientific title	Evaluation of the clinical and cost-effectiveness of a care pathway for patients with chronic pain after total knee replacement: STAR trial
11	Countries of recruitment	UK
12	Health condition(s) or problem(s) studied	Chronic pain after total knee replacement
13	Intervention(s)	Intervention group: One-hour STAR assessment clinic with an Extended Scope Practitioner to identify potential causes of pain and enable onwards referral to appropriate existing services. Up to 6 telephone follow-up calls from the Extended Scope Practitioner over the 12 month follow-up period. Control group: Care as usual
14	Key inclusion and exclusion criteria	Age: 18 years or over; no upper age restriction Sex: Male or female Inclusion: Patients who have received a primary total knee replacement because of osteoarthritis at a participating NHS Trust and who report pain in their operated knee at 2–3 months after surgery (score of 0–14 on the Oxford Knee Score pain subscale). Exclusion: A lack of capacity to provide informed consent to participate, previous participation in the STAR trial for the contralateral knee, participation in another research study that interferes unacceptably with the STAR trial
15	Study type	Interventional Allocation: Randomised Assignment: parallel Phase III
16	Date of first enrolment	October 2016
17	Target sample size	381
18	Recruitment status	Recruiting
19	Primary outcomes	Pain intensity and pain severity at 12 months after randomisation, measured using the Brief Pain Inventory
20	Key secondary outcomes	Brief Pain Inventory at 3 and 6 months after randomisation Oxford Knee Score at 3, 6 and 12 months after randomisation painDETECT at 3, 6 and 12 months after randomisation Douleur Neuropathique 4 at 3, 6 and 12 months after randomisation Hospital Anxiety and Depression Scale at 3, 6 and 12 months after randomisation Pain Catastrophizing Scale at 3, 6 and 12 months after randomisation Possible Solutions to Pain Questionnaire at 3, 6 and 12 months after randomisation Self-Administered Patient Satisfaction Scale at 3, 6 and 12 months after randomisation ICECAP-A at 3, 6 and 12 months after randomisation EQ-5D-5 L at 3, 6 and 12 months after randomisation SF-12 at 3, 6 and 12 months after randomisation

